**Figure 2 F2:**
[figure not shown]
DAMPAA Theory of Change from Mateo-Arriero *et al*.^38^ ACCO, Aboriginal Community-Controlled Organisations; AHP, Aboriginal Health Practitioner; DAMPAA, Dementia Prevention and Risk Management Program for Aboriginal Australians; KICA, Kimberley Indigenous Cognitive Assessment.

**Table 2 T2:** DAMPAA ToC assumptions and desired outcomes

DAMPAA ToC assumptions for resources to produce activities	DAMPAA ToC assumptions for activities to produce outcomes
Screening tool used is accepted and valid. Exercise professionals and AHPs are available for recruitment and running the programme. Exercise professionals and AHPs are appropriately trained to run the programme following the protocol.	Sufficient programme attendance from participants.Ability to come together safely for the group walking and yarning programme: Cultural safety. Health. COVID-19. Personal safety. Environment. Having the time, safe environment and space to complete the at-home exercise programme.Appropriate exercise level for participants.Appropriate content and delivery of the education, walking and yarning sessions.General practitioners enacting changes in medication based on pharmacist review.Setting achievable goals and participants taking action to reach said goals.

AHPAboriginal Health PractitionerDAMPAADementia Prevention and Risk Management Program for Aboriginal AustraliansToCTheory of Change

The DAMPAA ToC assumptions need to be met in order for the DAMPAA activities to produce the desired outcomes.^38^ These are shown in table 2.

#### Sample size

Based on unpublished analyses of a cohort study of ageing well,^7^ we expect KICA-Cog scores to decrease by a mean of 2 points in the usual care group, and by 1 point in the DAMPAA programme group, with a common SD of 3 points. A sample size of 286 people (143 in each group) would be required to provide 80% power to detect this difference, given a two-sided significance level of 5%. For the secondary outcome of daily function, we expect that 60% of the usual care group would have a decline in at least one activity of daily living during the study period, compared with only 44% of people in the DAMPAA programme arm. A sample size of 304 people would provide 80% power to detect such a difference at the 5% significance level. For the quality of life outcomes, based on previous research^35^ we expect mean GSGL and EQ-5D-5L scores to increase by 2 points and 1 point, respectively, in the DAMPAA group and to remain unchanged in the usual care group. Assuming a common SD of 3 points, a sample size of 74 and 286 people, respectively, is required to have 80% power to detect these differences at the 5% significance level. To account for potential attrition, we plan to recruit a total of 320 people (160 people per group).

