#### Outcomes

The primary outcomes will be cognition (measured by the KICA-Cog), daily function (measured by the KICA-Function tool) and quality of life (measured by the Good Spirit, Good Life (GSGL)^34 35^ andEQ-5D-5L tools.^44^ Secondary outcomes are described in table 1. Outcome measures will be recorded at baseline, 6 months and 12 months. Death will be followed-up with next of kin.

**Table 1 T1:** Secondary outcomes of the Dementia Prevention and Risk Management Program for Aboriginal Australians study

Secondary outcomes	Measure
Process outcomes (assumptions, resources and activities)	Yarning circles, surveys, in-depth interviews with staff members and participants
Death	Follow-up with next of kin
Cardiovascular risk factors	Resting mean systolic blood pressure (mm Hg). Mean cholesterol level (mmol/L). Glycosylated haemoglobin. Body weight, body composition and BMI (kg/m^2^). Waist and hip girths (cm). Smoking status – KICA smoking questionnaire. Alcohol intake – KICA alcohol questionnaire. Functional capacity (2 minute walk test). Regular physical activity - Rapid Assessment of Physical Activity. Medications – current medications and adherence.
Falls	Number of falls in previous 6 months

BMIbody mass indexKICAKimberley Indigenous Cognitive Assessment

Process outcomes will include the successful incorporation of (1) all DAMPAA ToC resources (figure 2) into the programme, (2) meeting of DAMPAA ToC assumptions (table 2) and (3) appropriate completion of ToC activities.^38^ These three steps will be explored through in-depth interviews with project staff and through surveys and/or yarning groups with participants.

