#### Randomisation and blinding

Participants will be randomised into the DAMPAA programme or usual care. Randomisation was performed with Stata SE V.15.1 (StataCorp, College Station, Texas, USA) using the ralloc package^45^ and was stratified by site. We aimed for a total of 140 allocations in each of the 3 strata, with 2 treatment arms, a 1:1 treatment allocation and 3 block sizes (varying between 6, 8 and 10). Block sizes were allocated in unequal proportions. Owing to the variable block size, the randomisation process yielded 434 unique study identifiers (n=148 for site 1, n=140 for site 2 and n=146 for site 3). An independent staff member from outside the study will be responsible for drawing out each participant’s ID for allocation to a group. AHP staff will enrol participants, and allocations to DAMPAA and usual care will be drawn from sealed envelopes by an external colleague independent of the study.

Psychologist assessors are blinded to the participant group and will not assess the same participant at multiple time periods. Project staff delivering the DAMPAA programme and conducting health and fitness assessments will not be blinded. At the conclusion of the trial, we plan to offer participants in the usual care group a chance to experience the DAMPAA programme, which will continue to be delivered by ACCOs.

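### The 80% power claimed for EQ-5D-5L (1 point, SD 3, 286 people) cannot be interpreted: the inputs do not fit the utility index or the visual scale, and no score is named

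*Protocol article*

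**What the plan says.** The Outcomes section of the protocol article puts quality of life among the primary outcomes: "quality of life (measured by the Good Spirit, Good Life (GSGL" is followed by EQ-5D-5L as the second instrument. The Abstract lists the same two tools.

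The Sample size section then powers each of them. For the programme group, "we expect mean GSGL and EQ-5D-5L scores to increase by 2 points and 1 point, respectively, in the DAMPAA group"; both scores are expected "to remain unchanged in the usual care group". The section continues: "Assuming a common SD of 3 points, a sample size of 74 and 286 people, respectively, is required". The stated target is 80% power at a 5% level. The expected changes are attributed to previous research (reference 35). Two-sided testing is stated earlier in the same section, for KICA-Cog ("given a two-sided significance level of 5"). The Randomisation and blinding section gives "2 treatment arms, a 1:1 treatment allocation".

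Nowhere does the article identify the EQ-5D-5L score, its range or its direction. The Neuropsychology assessments section says only that the tool measures health-related quality of life.

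**The concern.** A power statement needs a difference and an SD on the scale that will be analysed. EQ-5D-5L can be reported as a utility index, as a 0-100 visual scale, or as a sum of the five levels. These differ greatly in range, and the last runs in the opposite direction. A 1-point gain with an SD of 3 points does not look like the first two, and on the third an increase would normally mean worse health.

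The same SD of 3 is used for three instruments: KICA-Cog (scored out of 39 according to the Baseline assessments section), GSGL (12 factors) and EQ-5D-5L. No scale-specific reason is shown for this.

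What is at stake is how a null result on a primary outcome is read. A reader who takes the article at its word would regard a flat EQ-5D-5L result as coming from a comparison with 80% power for 1 point. On the index or the visual scale, that is not what 286 people provide.

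**Working it through.** **Inputs from the Sample size section:** difference 1 point for EQ-5D-5L (increase of 1 against 0) and 2 points for GSGL; SD 3 for both; 80% power; 5% two-sided. Allocation 1:1 is from Randomisation and blinding.

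**Step 1. Reproduce the stated figures.** With the normal approximation, n per arm = 2 × (1.960 + 0.842)² × (SD/difference)².
- EQ-5D-5L: 2 × 7.849 × 9 = 141.3, so 142 per arm (284). The exact two-sample t-test gives 142.25, so 143 per arm, **286 in total**, as stated.
- GSGL: 2 × 7.849 × 2.25 = 35.3, so 36 per arm (72). The t-test gives 36.3, so 37 per arm, **74 in total**, as stated.
- A one-sided test for EQ-5D-5L would give 224, so the two-sided level was used here too.

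The result depends only on the ratio 1/3. On any scale, 143 per arm detects with 80% power a difference of 2.802 × SD × √(2/143) = 0.331 × SD.

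**Step 2. Put the inputs on each candidate score.** The ranges, directions and SDs below are assumptions, because the article gives none.

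*Utility index, maximum 1.* A mean gain of 1 would need a starting mean of 0 or below and nearly everyone ending in full health. An SD of 3 is also out of reach. Changes on a scale of width R lie between −R and R, so their SD is at most R; an SD of 3 would need a scale reaching down to −2 or lower. The inputs cannot hold.

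*Visual scale, 0-100.* The 1-point difference is possible, but an SD of 3 is implausibly small. Power at 143 per arm follows from the noncentrality (1/SD) × √(143/2) = 8.456/SD, counting both tails:

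| Assumed SD | Noncentrality | Power for 1 point | Total N for 80% power | Detectable with 286 |
|---|---|---|---|---|
| 15 | 0.564 | 8.7% | about 7,060 | 5.0 points |
| 20 | 0.423 | 7.1% | 12,560 | 6.6 points |

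*Sum of levels, 5-25.* A 1-point difference needs 126 people at SD 2, 284 (286 by t-test) at SD 3 and 504 at SD 4. The stated inputs fit in size. On the usual coding a higher sum is worse health, so the expected increase is a benefit only if the score is reversed.

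**Step 3. What 286 analysed people can detect on the index.** 0.331 × SD gives 0.050, 0.066 and 0.083 for assumed SDs of 0.15, 0.20 and 0.25.

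**Step 4. Could analysing change, or adjusting for baseline, explain an SD of 3 on the visual scale?** With baseline adjustment the residual SD is SD × √(1 − ρ²), where ρ is the correlation between baseline and follow-up. To reach 3 from 15 needs √(1 − ρ²) = 0.20, so ρ = 0.98; from 20 it needs 0.15, so ρ = 0.99. For a change score, SD × √(2(1 − ρ)) = 3 leads to the same values, 0.98 and 0.99. Correlations that high over 6 to 12 months are not credible for a self-rated scale.

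**The case against.** The strongest reply is that nothing is miscalculated. The figure of 286 follows exactly from its inputs and is valid for a standardised difference of 0.33 on any scale. This stands. The fault lies in the inputs as expressed in points, and to call the power claim meaningless would go too far.

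A reader might also infer that the inputs fit no EQ-5D-5L score at all. The documents do not support that. A sum of levels can carry a 1-point difference and an SD of 3, and reverse scoring, or a loose use of increase for improvement, would settle the direction.

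A reader might infer that the KICA-Cog inputs were simply copied, since the difference, SD and total are identical. Equal numbers do not prove this. The section attributes the KICA-Cog assumptions to a cohort study and the quality-of-life changes to other research. That research is not at hand and may define the score.

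The score ranges and SDs used above come from outside the documents, which is why they are shown as assumptions with ranges. Naming the score and value set is also something that an article may leave to the full protocol or analysis plan, so that omission alone would be no finding. This article goes further: it publishes a difference, SD, sample size and power in unidentified points.

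Finally, the design does not rest on this figure. KICA-Cog independently gives 286, daily function gives the larger 304, and the target is 320. The Data management and analysis section describes KICA-Cog as the primary outcome measure. No one should conclude that the trial recruited too few people because of this statement.

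**Conclusion.** The point holds in a limited form. The stated 80% power for EQ-5D-5L is arithmetically correct for a standardised difference of 0.33 but not interpretable as 1 point. Under standard scoring, the inputs are impossible on the utility index. On the visual scale they would leave about 7% to 9% power for 1 point if the SD is 15 to 20. They suit the sum of levels only if that score is reversed.

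The conclusion rests on the assumed ranges and SDs, and on an unadjusted comparison of two means with 286 people analysed. It is a defect in a stated claim about a primary outcome, worth correcting before results are read against it. It does not put the sample size of the trial in doubt.

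**What to change.** In the Sample size section, or in the analysis plan with a cross-reference, replace the EQ-5D-5L statement of 1 point, SD 3 and 286 people. Name the score to be analysed and its direction, and give the difference that 286 analysed participants can detect with 80% power, using that score's own SD (about one third of it). As illustrations, this is about 0.05 to 0.083 on the index for assumed SDs of 0.15 to 0.25, or about 5.0 to 6.6 points on the visual scale for SDs of 15 to 20. Say whether the SD is of raw scores or of change.

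In the same edit, confirm that an SD of 3 applies to GSGL on its own scale, since the figure of 74 depends on it.

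The cost is one rewritten paragraph and, on the index or visual scale, a less favourable stated EQ-5D-5L figure. Recruitment, which closed in October 2023, is unaffected.

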#### Recruitment

Yarning workshops such as Elders yarning groups will be organised in collaboration with ACCOs to discuss the study for participant recruitment. Referral pathways with ACCOs will provide an opportunity for medical practitioners to refer interested clients to the DAMPAA team for follow-up. The DAMPAA programme will be explained in detail to participants at yarning workshops, highlighting the benefits and risks of taking part. Participants who agree to take part after meeting initial inclusion criteria will provide written informed consent to participate in the study. Participants can withdraw from the study at any time and this will be recorded with a participant withdrawal form. Forms are provided as online supplemental material 1.

#### Randomisation and blinding

Participants will be randomised into the DAMPAA programme or usual care. Randomisation was performed with Stata SE V.15.1 (StataCorp, College Station, Texas, USA) using the ralloc package^45^ and was stratified by site. We aimed for a total of 140 allocations in each of the 3 strata, with 2 treatment arms, a 1:1 treatment allocation and 3 block sizes (varying between 6, 8 and 10). Block sizes were allocated in unequal proportions. Owing to the variable block size, the randomisation process yielded 434 unique study identifiers (n=148 for site 1, n=140 for site 2 and n=146 for site 3). An independent staff member from outside the study will be responsible for drawing out each participant’s ID for allocation to a group. AHP staff will enrol participants, and allocations to DAMPAA and usual care will be drawn from sealed envelopes by an external colleague independent of the study.

Psychologist assessors are blinded to the participant group and will not assess the same participant at multiple time periods. Project staff delivering the DAMPAA programme and conducting health and fitness assessments will not be blinded. At the conclusion of the trial, we plan to offer participants in the usual care group a chance to experience the DAMPAA programme, which will continue to be delivered by ACCOs.

#### Data management and analysis

Data will be stored securely on a protected University of Western Australia (UWA) Institutional Research Data Store. Data will be de-identified to maintain confidentiality. All quantitative data will be entered and analysed using the Stata statistical package, while qualitative data will be managed with NVivo (Lumivero, Denver, Colorado). The study will employ an intention-to-treat analysis including all randomised participants. This means that participants will be analysed as per their randomisation, rather than the treatment they ultimately receive. We will use a generalised linear mixed model to compare changes in the KICA-Cog (cognition, primary outcome measure) over time between the two groups, with a significantly greater decrease in KICA-Cog scores expected in the usual care group at 12 months. The covariates in this model will be the baseline KICA-Cog score, time (6 or 12, entered as a categorical variable), group (DAMPAA programme or usual care) and an interaction between group and time. Participant and site will be treated as random effects. Similar models will be run for the other outcomes which are a mixture of variable types (proportions, counts, etc). We will handle missing data by performing complete case analyses. Results will be reported in accordance with the Consolidated Standards of Reporting Trials statement.^46^

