Aboriginal health research occurs in complex contexts that present a unique number of organisational and community challenges.^36^ Staff shortages and absences, as well as high workforce turnover, particularly outside urban settings, are common challenges.^37^ Challenges for researchers include managing a project across distant locations, low recruitment numbers and providing an appropriate level of support to Aboriginal research staff to successfully carry out project objectives.^37^ Participant challenges to involvement in research include family commitments, attending funerals, caring for grandchildren, transport and other medical appointments which make it more difficult to prioritise commitments to a programme.^38^ In addition, dementia risk factor awareness in the Aboriginal community is low.^39^ Participant enablers for adherence to physical activity programmes include location and attending an Aboriginal centre with other Aboriginal people, transport assistance, enjoyment in programme activities and feeling healthy.^29 40 41^ A clear programme structure, access to varied exercise equipment and learning about health are also factors that enable increased adherence.^42^

A multi-domain, culturally safe and responsive programme specifically targeting modifiable risk factors to reduce cognitive decline in older Aboriginal people is required. Key principles for successful research with Aboriginal people include leadership and ownership by Aboriginal researchers, local development, commitment, control, supporting workers’ professional development, Aboriginal community capacity building and facilitating enablers to increase community participation.^29 37 42 43^

This paper describes the protocol for the Dementia Prevention and Risk Management Program for Aboriginal Australians (DAMPAA), co-designed to address the modifiable risk factors for dementia in Aboriginal people. The first participant was enrolled in October 2020 and the last enrolment was October 2023. Data collection will conclude in late 2024.

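### The complete-case rule sits badly with an analysis of all randomised participants and, read literally, discards 6-month scores that the planned mixed model could use

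*Protocol article*

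**What the plan says.** All the relevant statements on method stand in one paragraph of the protocol article, Data management and analysis.

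- Population: "The study will employ an intention-to-treat analysis including all randomised participants". The next sentence explains this as analysis by randomised arm rather than by treatment received.
- Model: "We will use a generalised linear mixed model to compare changes in the KICA-Cog (cognition, primary outcome measure) over time between the two groups". On its terms: "The covariates in this model will be the baseline KICA-Cog score, time (6 or 12, entered as a categorical variable), group", plus a group-by-time interaction. "Participant and site will be treated as random effects".
- Missing data: "We will handle missing data by performing complete case analyses". The article names no other method and no missingness assumption.

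Under Outcomes, the schedule is: "Outcome measures will be recorded at baseline, 6 months and 12 months". Under Sample size, 320 people are to be recruited against requirements of 286 (KICA-Cog) and 304 (daily function), to allow for attrition at a rate that is not stated.

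**The concern.** This is not a gap that an analysis plan might fill. The article names a missing-data method, and that method fits poorly with two other statements in the same paragraph.

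First, once anyone is lost, a complete-case set is not all randomised participants, and the sample-size section expects some loss. Second, a likelihood fit of a model with two follow-up times and a participant random effect can keep the 6-month score of someone who misses month 12. It is valid if missingness depends on scores already observed. Removing that person discards the score. The 12-month contrast is then valid only if loss does not depend on decline since baseline, or depends on it in a way that cancels between arms. Adjusting for baseline does not repair this.

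Loss could plausibly differ by arm. DAMPAA participants have transport, reminder calls and regular contact, but also up to 270 minutes of activity a week. Usual care has a mailed pamphlet and the two follow-up assessments. The Background lists general obstacles to taking part: "family commitments, attending funerals, caring for grandchildren, transport and other medical appointments". None of this settles which arm loses more people, or whether those lost are the ones who declined.

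**Working it through.** **The plan's own figure.** The sample-size section states: "we expect KICA-Cog scores to decrease by a mean of 2 points in the usual care group, and by 1 point in the DAMPAA programme". It takes SD 3, 80% power and a two-sided 5% level. Per group, n = 2 × (1.960 + 0.842)² × 3² / 1² = 141.3, so 142 (284 in total). The t-test version gives 142.2, so 143 per group, or 286. The stated 286 reproduces.

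**Margin for loss.** 1 − 286/320 = 10.6% and 1 − 304/320 = 5.0%. If only complete cases count and 20% are lost, 128 per arm remain. The standard error is 3 × √(2/128) = 0.375, and 1/0.375 − 1.960 = 0.707, so KICA-Cog power is about 76%.

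**Inputs for the bias check.** From the protocol: true 12-month difference 1.0 (mean changes −2 and −1) and SD 3. Assumed, because the protocol gives nothing: mean 6-month changes −1.0 (usual care) and −0.5 (DAMPAA), SD 3 at 6 months, normal changes, 6-to-12-month correlation ρ = 0.6, and everyone seen at 6 months. Where 12-month loss depends on decline, logit(loss) = −1.6 − 0.3 × (6-month change + 1).

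**Formula.** With equal SDs, the regression of 12-month on 6-month change has slope ρ. Completers' 12-month mean is therefore off by ρ × s, where s is the amount by which completers' mean 6-month change exceeds that of the whole arm. Hence

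complete-case estimate = 1.0 + ρ × (s in DAMPAA − s in usual care).

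Integrating the dropout model over each arm's normal distribution gives 20.1% loss and s = 0.481 in usual care, and 18.0% loss and s = 0.434 in DAMPAA.

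| Pattern of 12-month loss | Calculation | Complete-case estimate |
|---|---|---|
| Depends on decline in usual care only; 12% at random in DAMPAA | 1 + 0.6 × (0 − 0.481) | 0.71 |
| Depends on decline in DAMPAA only; same model | 1 + 0.6 × (0.434 − 0) | 1.26 |
| As above, DAMPAA loss raised to 20.1% (s = 0.481) | 1 + 0.6 × (0.481 − 0) | 1.29 |
| Same model in both arms | 1 + 0.6 × (0.434 − 0.481) | 0.97 |
| Same slope on decline, loss 20% usual care and 12% DAMPAA (s = 0.479 and 0.297) | 1 + 0.6 × (0.297 − 0.479) | 0.89 |
| Unrelated to decline in either arm, any rates | 1 + 0.6 × (0 − 0) | 1.00 |

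**Range.** Large simulations varied ρ between 0.5 and 0.7 and loss between 10% and 30%.

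- Dependence in usual care only: 0.51 to 0.87.
- Dependence in DAMPAA only: 1.13 to 1.48.
- One shared model, with log-odds of loss 0.3 to 0.6 per point of decline: 0.91 to 0.98.

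The likelihood estimate, which regresses 12-month on 6-month change among completers and applies the result to everyone's 6-month data, stayed between 0.99 and 1.02 throughout.

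**The case against.** Three objections carry weight.

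The wording may be loose. In a mixed model, complete case can mean only that rows without an outcome are omitted and nothing is imputed. Someone with a 6-month score then stays in, the estimate is valid under missing at random, and the bias above does not arise. The text does not exclude this reading, but it does not state it either. Two analysts could follow the sentence differently and report different primary estimates.

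The protocol also explains intention to treat as analysis by allocated arm, and restricting to observed outcomes does not breach that. A reader might infer that the two sentences flatly contradict each other. The documents support less: the conflict is with the promise to include all randomised participants. That promise fails even on the lenient reading, because with baseline as a covariate a person with no follow-up score contributes nothing.

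The size is conditional. A reader might infer from the 0.71 that the trial will understate its effect by about 29%. Nothing in the protocol supports dependence on decline in one arm alone. The listed obstacles to participation are mostly not evidently linked to cognitive decline, and transport and reminder calls are described as aids to programme adherence, not to attendance at assessments. Unequal loss by itself gives no bias if it is random, and the direction can reverse.

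**Conclusion.** The point holds as a should-fix. The protocol names a missing-data rule that, taken literally, is inferior to the model it accompanies and cannot deliver the stated analysis population. Under the assumed inputs the 12-month estimate could fall anywhere from about 0.7 to about 1.3 against a true 1.0 when dependence on decline is confined to one arm. It is about 0.97 under a shared dropout model and 1.00 when loss is unrelated to decline. The correlation, the loss rates and the dropout slope are assumptions; only the difference of 1, the SD of 3 and the sample sizes come from the protocol. The advantage of using all visits also assumes missing at random given the observed scores.

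A must-fix grading is not supported: the bias is not shown to be present, its direction is unknown, and the intended meaning may already be the lenient one. The absence of detailed imputation or sensitivity plans is not counted here, since an analysis plan may hold them.

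**What to change.** Replace the missing-data sentence with wording such as: *Every observed 6- and 12-month score from each randomised participant enters the likelihood-based mixed model, analysed by allocated arm, under the assumption that data are missing at random. No participant is excluded for missing one visit. A complete-case analysis will be reported as a sensitivity analysis.*

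Reword the population statement so that it can be met. Either say that participants with no post-baseline score do not contribute when baseline is a covariate, and report their number by arm, or model baseline as an outcome alongside months 6 and 12 so that they do.

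Preferably add one sensitivity analysis in which missing 12-month KICA-Cog scores are shifted separately by arm, since missing at random cannot be checked from the data.

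The cost is a few sentences and a little Stata code, with no new data. The change should be recorded before any comparison by group is run, so that the reading of complete case is not chosen after the results are known.
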